## Abstract

**Background:**

Currently, a cervical esophagogastric anastomosis (CEA) is often performed after minimally invasive esophagectomy (MIE). However, the CEA is associated with a considerable incidence of anastomotic leakage requiring reintervention or reoperation and moderate functional results. An intrathoracic esophagogastric anastomosis (IEA) might reduce the incidence of anastomotic leakage, improve functional results and reduce costs. The objective of the ICAN trial is to compare anastomotic leakage and postoperative morbidity, mortality, quality of life and cost-effectiveness between CEA and IEA after MIE.

**Methods/design:**

The ICAN trial is an open randomized controlled multicentre superiority trial, comparing CEA (control group) with IEA (intervention group) after MIE. All patients with esophageal cancer planning to undergo curative MIE are considered for inclusion. A total of 200 patients will be included in the study and randomized between the groups in a 1:1 ratio. The primary outcome is anastomotic leakage requiring reintervention or reoperation, and secondary outcomes are (amongst others) other postoperative complications, new onset of organ failure, length of stay, mortality, benign strictures requiring dilatation, quality of life and cost-effectiveness.

**Discussion:**

We hypothesize that an IEA after MIE is associated with a lower incidence of anastomotic leakage requiring reintervention or reoperation than a CEA. The trial is also designed to give answers to additional research questions regarding a possible difference in functional outcome, quality of life and cost-effectiveness.

**Trial registration:**

Netherlands Trial Register: NTR4333. Registered on 23 December 2013.

## Background

The annual incidence of esophageal carcinoma is increasing [1]. Anastomotic leakage is an important early postoperative complication that often results in reoperation, delayed (ICU) discharge, psychological distress and associated costs. Leak rates cited in the recent literature range from 0–30 % [2, 3], and anastomotic leakage is the main cause of postoperative mortality. It is estimated to be responsible for up to 40 % of deaths following esophagectomy and is associated with a prolonged ICU treatment and hospital stay [3, 4]. Late complications, such as anastomotic stricture, are also responsible for significant morbidity. Stricture rates following esophageal anastomosis range from 5–40 % [5].

In current practice, both intrathoracic esophagogastric anastomosis (IEA) and cervical esophagogastric anastomosis (CEA) are used worldwide to restore gastrointestinal continuity after esophagectomy with gastric tube reconstruction. Four randomized controlled trials including a total of 267 patients have been performed that compared the results of CEA with IEA after open esophagectomy [2]. The mean incidence of anastomotic leakage was 26 % after CEA and 4 % after IEA. No significant differences between the groups were found for mortality, pulmonary complications or hospital stay.

However, all trials performed so far have serious methodological flaws. All trials are single centre studies including a limited number of 32 to 92 patients, of whom a substantial number was either excluded from the analysis for unclear reasons or not reported. Furthermore, allocation concealment was not always reported and intention-to-treat analyses not performed. All studies were performed before neoadjuvant chemoradiotherapy was introduced, and none of the studies included patients undergoing minimally invasive esophagectomy (MIE). Finally, data on quality of life, functional results and cost-effectiveness have not been studied.

Therefore, the results of the previous trials are difficult to interpret and may not be applicable to current surgical practice. Since high-quality evidence is lacking, there are no (inter)nationally accepted evidence-based guidelines for the preferred location of the esophagogastric anastomosis.

## Methods/design

### Study aim

The aim of the ICAN trial is to compare anastomotic leakage and postoperative morbidity, mortality, quality of life and cost-effectiveness between CEA (control group) and IEA (intervention group) after MIE.

### Design and setting

The ICAN trial is designed as an open randomized, multicentre superiority trial. Patients are randomly allocated to undergo MIE with CEA or IEA (Table 1). The study will be conducted in Dutch hospitals with surgeons who are competent in performing both techniques.

**Table 1 Tab1:** Schedule of enrolment, interventions and assessments

		Study period					
	Enrolment and allocation	Post-allocation					Close-out
Timepoint (months)		Surgery	Follow-up after surgery				
	0	1	2.5	4	7	13	25
Enrolment:							
Eligibility screen	X						
Informed consent	X						
Allocation	X						
Interventions:							
MIE with cervical anastomosis		X					
MIE with intrathoracic anastomosis		X					
Assessments:							
Baseline patient characteristics	X						
Baseline tumour characteristics	X						
QOL questionnaires	X		X	X	X	X	X
CE questionnaires	X			X	X	X	X
Postoperative outcome data		X					
Pathology data		X					
Functional recovery data		X	X	X	X	X	X
Oncologic follow-up data			X	X	X	X	X

*QOL* quality of life, *CE* cost-effectiveness

### Primary endpoint

The primary endpoint is anastomotic leakage for which endoscopic, radiologic or surgical reintervention is needed. This corresponds to the Esophagectomy Complications Consensus Group (ECCG) definition of anastomotic leakage type II and type III [6]. Anastomotic leakage is defined according to the ECCG [6] as a full thickness defect of the anastomosis. This can be identified by (1) computed tomography (CT) scan with intravenous and oral contrast (’swallow CT scan’), (2) endoscopy, (3) drainage of ingested materials into the chest tube (intervention group) or ingested materials or saliva into the cervical wound (control group) or (4) established anastomotic leakage during reintervention, reoperation or autopsy. Anastomotic leakage is assessed during treatment by the treating surgeon and a member of the ICAN study team. In addition, a third ICAN study team member will assess anastomotic leakage using blinded medical reports. Leakages of the gastric tube are scored separately and will be reported separately. If the location of a leak is uncertain (anastomosis or gastric tube), but it has been shown that a leak is present, this is scored as anastomotic leakage.

### Secondary endpoints

Secondary endpoints are incidence of postoperative complications (i.e. pneumonia, pneumothorax, pleural empyema, mediastinal abscess, cardiac complications), severity of complications according to the modified Clavien-Dindo classification [7] and new onset organ failure according to the Sepsis-related Organ Failure Assessment (SOFA) score [8]. General quality of life is scored by EuroQol 5D, whereas cancer-specific quality of life is assessed with the European Organization for Research and Treatment of Cancer Quality of Life Questionnaire (EORTC-QLQ C30). To assess esophageal cancer-specific quality of life, the EORTC-QLQ OG25 module is used. From the questionnaires, the domains of general quality of life and eating-related quality of life are the most important outcomes, although all domains of the questionnaires will be assessed.

Functional outcome parameters, including dysphagia, regurgitation, weight loss, return to preoperative weight and the incidence of benign strictures requiring dilatation are also scored. Other secondary endpoints are hospital mortality, mortality after 30 and 90 days, length of stay in the ICU and in the hospital, ICU and hospital readmission rate, the incidence of recurrent laryngeal nerve trauma and cost-effectiveness.

### Population

All patients with resectable esophageal carcinoma are screened for eligibility by their esophageal surgeon.

### Inclusion criteria

Inclusion criteria are age ≥18 years and histologically proven primary esophageal adenocarcinoma or squamous cell carcinoma. Patients are only included if the tumour is considered resectable (cT1b-4a, N0-3, M0) and the bulk of the tumour is located in the distal or mid esophagus (distal to the level of the carina) or at the level of the cardia-esophageal junction (up to Siewert II [9]).

### Exclusion criteria

Exclusion criteria are previous major gastric or major thoracic surgery rendering MIE unfeasible, prognosis determining malignancy other than esophageal cancer, inability to undergo curative resection and/or follow-up and inability to provide oral or written informed consent.

### Time of inclusion and randomization

In the Netherlands, most patients with resectable tumours are scheduled to undergo neoadjuvant chemoradiotherapy, which is completed approximately 8 weeks before surgery. Patients will be given information about the trial and will be randomized after neoadjuvant chemoradiotherapy or in the weeks before surgery if neoadjuvant chemoradiotherapy is not indicated.

### Randomization

Patients will be randomized to the intervention group or the control group with a 1:1 ratio, using a computerized randomization tool (Castor [10]). Patients are stratified according to hospital in order to ensure that other local treatment factors (i.e. postoperative care) are unlikely to interfere with study outcome. Permuted-block randomization with varying block size is used. Allocation and block size are concealed to all investigators. Because of the nature of this trial involving different surgical incisions, blinding treating surgeons and trial participants is unfeasible: A patient will feel whether a cervical incision has been made, and the surgeon knows which operation has been performed. However, a study team member will assess blinded medical reports regarding anastomotic leakage in order to obtain blinded assessment of the primary outcome parameter.

Patients can withdraw from the study at any time. The operating surgeon can decide not to perform a resection during surgery if the tumour is found to be irresectable because of ingrowth into adjacent organs, if perioperative metastases to other organs are found or if resection is unfeasible because of other perioperative events or findings. Modification of the intervention during surgery is justified if the operating surgeon decides he is unable to perform the allocated anastomosis. In this case, follow-up continues according to the trial protocol, and an intention-to-treat analysis will be performed.

### Operative technique

All patients will be scheduled to undergo MIE with IEA or CEA. For both treatment arms, an identical two-field lymphadenectomy is performed, and a gastric tube reconstruction with the gastric tube in the posterior mediastinum is used. An omental wrap is performed after IEA and CEA, since there is evidence that this reduces the incidence of clinically relevant anastomotic leakage [11]. Other surgical factors are left to the discretion of the surgeon.

### Quality control of operative technique

To prevent learning curve bias, only surgeons who have performed at least 50 minimally invasive intrathoracic anastomoses and >50 cervical anastomoses can participate in this trial. To ensure the quality in each participating centre, a surgical procedure is recorded upon trial participation to evaluate the quality control of the operation. This recording was evaluated by an expert group of 10 other dedicated minimally invasive esophageal surgeons. During this meeting, this group of experts also discussed the results of MIE with CEA and MIE with IEA over the last 2 years per participating centre. Hospitals and their surgeons can only participate in the study if the experts judged both the surgical procedure and the results of the last 2 years as satisfactory. This expert opinion-based approach was used because there is currently no consensus on how surgical proficiency should be determined. Furthermore, a video will be recorded of each included patient. To ensure operative quality during the trial, the principal investigator (PI) or one of the lead investigators will evaluate the video of every fifth randomized patient. To prevent institution-related bias, only hospitals with a high volume (>30 esophagectomies per year) are invited to participate, and randomization will be stratified per hospital.

### Data collection and data management

At inclusion, a participant number will be generated, and this number will be used for further identification in the database. The participant number key is accessible by the PI and coordinating investigator. Clinical data will be collected by the study coordinator or research nurse and will be recorded in a good clinical practice (GCP)-compliant digital case record form (CRF) and database (Castor [10]). All non-electronic items containing data are kept in locked cabinets at the data coordinating centres. The data can be accessed by the research nurse, research physician and PI. Participating centres can request information from the database, but will only have access to their own centre’s data. After the study has been completed, requests to access the dataset can be submitted to the PI. The completed CRFs will also be checked with the source data regarding the primary outcome parameter and important secondary outcome parameters.

### Follow-up

For each participant, the study will start at randomization and the subject will be followed until 24 months after surgery. The primary outcome parameter will be evaluated 3 months after surgery. During the remaining 21 months of the follow-up, data on readmission, functional results, quality of life and cost-effectiveness will be generated. Study visits are scheduled to take place 2 weeks before surgery, 6 weeks after surgery and after 3, 6, 12 and 24 months.

### Strategies to improve adherence to recruitment and intervention protocols

Surgeons and local research nurses will receive email messages 1–2 days before an eligible patient visits their outpatient clinic. Inclusion rate feedback will be provided every 3 months in an electronic newsletter. Completeness of CRF data and the adherence to study protocol will be checked on a weekly basis by the coordinating investigator or research nurse, in addition to the monitoring procedure. A yearly investigators meeting will be held.

### Safety and monitoring

An independent data safety monitoring committee (DSMC) will evaluate the progress of the trial and will examine safety variables. The DSMC consists of a surgeon, a randomized controlled trial specialist and a statistician. Individualized patient description charts including safety parameters will be presented to the DSMC including one table comprising these endpoints in blinded groups for every 30 patients. The main safety parameters are all serious adverse events (SAEs) and include mortality, multiple organ failure, anastomotic leakage, pulmonary complication rate, cardiovascular complication rate, reinterventions and reoperation.

After the investigators have presented the data, the members of the DSMC will discuss these results in the absence of the investigators and will then advise them. Possible options will include continuing the trial, performing an interim analysis, adjusting the trial’s design and discontinuing the trial. Discontinuation will be advised if the DSMC concludes that the results would convince a broad range of clinicians that one trial arm is inferior or if safety is compromised in one arm. If the DSMC advises to adjust the trial’s design, to perform an interim analysis or to discontinue the trial, the responsible medical ethical committee will also be notified. SAEs will be reported to the Central Committee on Research involving Human Subjects using an online module [12].

The ICAN trial will be monitored according to the Dutch federation of universities guidelines. Since both interventions that are being investigated are considered to be standard care in the Netherlands, this is a low-risk study. The conduction of the trial will be monitored in two visits per participating site, and the monitor will check trial processes in 5 % of the included patients.

### Sample size calculation

The incidence of anastomotic leakage requiring reintervention or reoperation (type II or III [6]) after CEA is estimated to be 25 % [2, 13], and this is estimated to be 10 % after IEA [2, 3]. This estimation also corresponds to data from our own database in which data on morbidity after esophageal resection is collected from three of the participating hospitals, and this difference is considered to be clinically relevant. Based on a superiority trial design and taking an alpha of 0.05 and a power of 80 %, 100 patients per treatment arm should be included.

### Statistical analysis

Analyses will be carried out according to the intention-to-treat principle. For dichotomous data, frequencies will be presented, and continuous data will be presented as mean and standard deviation or median and range. The main outcome parameter in the two groups will be compared by calculating both the risk difference and relative risks with their 95 % confidence intervals. An additional per-protocol analysis will be done to evaluate the effectiveness of the intervention with regard to the actual treatment received. Differences in quality of life (as scored by the validated EuroQol 5D, EORTC-QLQ C30 and EORTC-QLQ OG25 questionnaires) will be analysed using a Mann-Whitney test.

Subgroup analysis will be performed on the type and configuration of anastomosis (i.e. side-to-end, side-to-side or end-to-end). Further subgroup analysis will only be carried out in case of significant interaction effects. Potential modification of the effect of each intervention will be evaluated with Poisson analyses.

Patients with open and closed procedures are replaced with new subjects. In the case of missing data, we will perform Poisson regression analyses with a robust covariance matrix estimator to adjust for covariates, since it has been shown that complete case analysis with covariate adjustment and multiple imputation yield similar estimates in the event of outcome data that are missing at random [14]. In addition, we will perform a sensitivity analysis in which a complete case analysis is compared to the multiple imputation analysis, in order to investigate whether multiple imputation would lead to different results.

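### Randomisation is stratified by hospital, but the stated primary comparison names no hospital term and mentions covariate adjustment only for missing data: a small, avoidable loss of precision.

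*Protocol article*

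**What the plan says.** The Randomization section of the protocol article makes hospital the stratification factor: "Patients are stratified according to hospital". The reason given is that local care, such as postoperative care, could otherwise affect the outcome. It adds: "Permuted-block randomization with varying block size is used". The section on quality control of operative technique repeats the factor as a guard against institution-related bias: "randomization will be stratified per hospital".

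The Statistical analysis section gives the primary comparison in one sentence: "The main outcome parameter in the two groups will be compared by calculating both the risk difference and relative risks", each with a 95% confidence interval. It names no hospital term and no test, and does not say which measure decides superiority. Covariate adjustment appears later in the same section, in connection with missing data: "In the case of missing data, we will perform Poisson regression analyses with a robust covariance matrix estimator to adjust for covariates". The covariates are not listed. The only other use of Poisson models there is to examine effect modification.

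**The concern.** The sponsor stratifies because it expects hospital to matter, but the stated comparison does not carry hospital through. Stratified blocks remove chance imbalance between arms in hospital mix. An unadjusted standard error still counts the variation between hospitals as noise, so it is too large whenever leak rates differ between them. The sponsor pays for stratification in logistics and does not collect the precision.

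The place where adjustment does appear adds to this. Stratified randomisation is a reason to adjust in every case, whereas missing data are a weak reason to begin adjusting. In addition, a superiority trial that lists two intervals without ranking them has no fixed rule for the borderline case in which one excludes the null and the other does not.

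**Working it through.** **Inputs from the article.** Leak rates of 25% (cervical) and 10% (intrathoracic), alpha 0.05, power 80%, 100 per arm (Sample size calculation); 1:1 allocation in blocks within hospital (Randomization).

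**Assumed, not in the documents.** Number of hospitals (5 or 8, of equal size) and the between-hospital standard deviation (SD) of the log-odds of leakage (0 to 1.0). For scale, hospitals one SD above and one SD below average differ by an odds ratio of e^(2×0.5) = 2.7 at SD 0.5, and e^(2×1.0) = 7.4 at SD 1.0.

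**1. The plan's own figure.** Two-sided test of two proportions, pooled variance, no continuity correction, mean rate 0.175:

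n = [1.960·√(2·0.175·0.825) + 0.842·√(0.25·0.75 + 0.10·0.90)]² / 0.15² = (1.053 + 0.443)² / 0.0225 ≈ 99.5, so 100 per arm.

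This matches, with power 80.2% at 100 per arm. The planned size therefore rests on an unstratified test.

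**2. Why the unadjusted interval is too wide.** With N per arm, K equal hospitals and m = N/K per arm in each:

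- Unadjusted SE = √{[p₁(1−p₁) + p₂(1−p₂)]/N}
- Stratified SE = (1/K)·√{Σₕ[p₁ₕ(1−p₁ₕ) + p₂ₕ(1−p₂ₕ)]/(m−1)}

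With equal, balanced hospitals the two estimates of the risk difference are identical and only the SEs differ. Within an arm, p(1−p) equals the average of pₕ(1−pₕ) plus the variance of pₕ between hospitals. The unadjusted SE keeps that last term although stratification has removed it from the comparison.

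**3. Size, 5 hospitals of 20 per arm, 40,000 simulated trials per setting.** Average rates are held at 17.5% in both arms (type I error and SE) or at 25% and 10% (power).

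| SD of log-odds | Type I error, unadjusted | Type I error, stratified | Power, unadjusted | Power, stratified | Unadjusted/stratified SE |
|---|---|---|---|---|---|
| 0 | 5.3% | 5.2% | 81.6% | 81.6% | 0.0534/0.0536 = 1.00 |
| 0.3 | 5.0% | 5.1% | 81.5% | 81.7% | 0.0532/0.0532 = 1.00 |
| 0.6 | 4.7% | 5.2% | 81.6% | 82.6% | 0.0530/0.0521 = 1.02 |
| 1.0 | 4.2% | 5.3% | 81.9% | 84.3% | 0.0522/0.0497 = 1.05 |

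Power lost: 82.6 − 81.6 = 1.0 point at SD 0.6, and 84.3 − 81.9 = 2.4 points at SD 1.0.

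**4. Size, 8 hospitals of 12 per arm (192 patients), average rates again held at 25% and 10%.** Power was 79.9% unadjusted against 80.5% stratified at SD 0.5, and 80.4% against 82.9% at SD 1.0: losses of 0.6 and 2.5 points. The stratified/unadjusted interval widths were 0.989 and 0.948, so the unadjusted interval is 1/0.989 = 1.011 and 1/0.948 = 1.055 times as wide.

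**5. Two measures, none decisive.** Take 20/100 against 10/100 leaks:

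- Risk difference: SE = √(0.20·0.80/100 + 0.10·0.90/100) = 0.050. The interval is −10.0 ± 1.96·5.0, or −19.8 to −0.2 points, which excludes 0.
- Relative risk: SE of the log = √(1/20 + 1/10 − 2/100) = 0.361. The interval is 0.50·exp(±1.96·0.361), or 0.25 to 1.01, which includes 1.

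Exact enumeration at 100 per arm and the planned rates gives power of 81.6% by risk difference and 79.7% by relative risk, with disagreement in 1.9% of trials. With equal rates of 10 to 25%, disagreement is 0.6 to 1.1%. Claiming success if either interval excludes the null gives type I error of 5.1 to 5.2%, the same as the risk difference alone.

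**The case against.** The strongest objection is that this is only silence. The article does not call the comparison unadjusted, both measures can be computed with a hospital adjustment, and a full protocol or analysis plan that is not shown may specify one. It stands that the word crude would be an inference. It does not dispose of the point, because the article does mention covariate adjustment, and only for missing data. Accounting for the stratification factor in every case is therefore a specific improvement to the stated text.

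Three stronger readings are tempting, and the document supports none of them.

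- A reader might infer that ignoring the strata makes the inference invalid. The error is conservative: unadjusted type I error is at or slightly below 5% when hospitals differ.
- A reader might infer that the trial becomes underpowered. That appears only if the simulated average rates drift from the planned ones. Centring hospitals at the log-odds of 25% and 10% with SD 1.0 moves the average rates to 28.6% and 13.4%, and unadjusted power to 76.0% with 192 patients. With the averages held at 25% and 10%, it stays at about 80 to 82%.
- A reader might infer that one missing outcome replaces the primary model. The Poisson sentence sits beside a multiple-imputation sensitivity analysis and can equally be read as missing-data handling. The text does not say that the risk difference and relative risk are withdrawn.

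It also stands that entry is limited to high-volume, vetted centres, which makes an SD of 1.0 less plausible, though not excluded. Reporting an absolute and a relative effect together is ordinary good practice.

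**Conclusion.** The point holds as a modest one. Hospital is built into the randomisation and absent from the stated primary comparison. For 5 to 8 equal hospitals with a log-odds SD of 0.5 to 1.0 and average rates at the planned values, the cost is an interval about 1 to 6% too wide, a type I error of about 4 to 5%, and about 1 to 3 points of power. The direction is certain if hospitals differ. The size rests on the assumed number of hospitals and spread, and it is nil if they do not differ.

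The missing choice between risk difference and relative risk is a lesser matter. Both test the same null hypothesis, and they disagree in about 2% of trials at the planned rates. It is worth settling in advance only because a borderline result would otherwise be open to argument.

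**What to change.** State that the primary comparison accounts for hospital whether or not data are missing. Either of two routes will do:

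- a Mantel-Haenszel risk difference with its 95% interval and a Cochran-Mantel-Haenszel test at two-sided 5%; or
- the robust Poisson model already named in the Statistical analysis section, with arm and hospital as terms.

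Set a fixed rule, before the data are seen by arm, for pooling hospitals that contribute very few patients. Name one measure as decisive and report the other as supportive. The choice between them is the sponsor's; the Mantel-Haenszel route is the closest stratified counterpart of the test behind the sample size. The unadjusted counts and percentages can stay as description.

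The cost is a few sentences of analysis text. The 100 patients per arm do not change, since the stratified analysis has about the same power as the unadjusted one when hospitals are alike and more when they differ.

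### The only method named for comparing quality of life, a Mann-Whitney test, makes poor use of a baseline and five follow-up measurements; a baseline-adjusted repeated-measures model would be more precise and less exposed to selective non-response

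*Protocol article*

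**What the plan says.** All of this is in the protocol article.

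- **Measurement.** Table 1 (Design and setting) marks the row "QOL questionnaires" at months 0, 2.5, 4, 7, 13 and 25, with surgery at month 1. The Follow-up section agrees: "Study visits are scheduled to take place 2 weeks before surgery, 6 weeks after surgery and after 3, 6, 12 and 24 months". That is one pre-operative and five post-operative assessments.
- **Priority.** Under Secondary endpoints, "the domains of general quality of life and eating-related quality of life are the most important outcomes", though every domain will be assessed. No visit is singled out.
- **Comparison.** Under Statistical analysis, scores from the EuroQol 5D, the QLQ-C30 and the "OG25 questionnaires) will be analysed using a Mann-Whitney test". No other method for quality of life appears. A risk difference and relative risk with 95% confidence intervals are promised for the main outcome. Continuous data get descriptive summaries by mean and SD or median and range.
- **Missing data.** The same section says: "In the case of missing data, we will perform Poisson regression analyses with a robust covariance matrix estimator to adjust for covariates". It adds a sensitivity analysis in which "a complete case analysis is compared to the multiple imputation analysis". Neither sentence names an outcome.

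**The concern.** Quality of life is part of the stated study aim, and the trial goes to the trouble of measuring it six times per patient. A two-sample rank test does not match that design. It compares one number per patient between two groups. It has no place for the baseline score, for hospital (the randomization stratum) or for the correlation among a patient's own visits. Its usual output is a p-value, and the text promises no between-arm difference in scale points with an interval.

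The test also has no means of using a patient whose value is missing. Over 24 months after resection for esophageal cancer, those who return forms are likely to become fewer and less representative. A model that uses each patient's earlier scores can recover part of that information; a rank test on the responders cannot.

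At stake are the precision and usability of a leading secondary result that the Discussion expects to inform guidelines. The primary result is not at stake.

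**Working it through.** **1. The plan's own figure.** The only sample size given is for leakage: "after CEA is estimated to be 25" per cent, against 10% after IEA, "taking an alpha of 0.05 and a power of 80 %, 100 patients per treatment arm should be included". With a pooled two-sided test and mean rate 0.175:

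n = [1.96 × √(2 × 0.175 × 0.825) + 0.8416 × √(0.25 × 0.75 + 0.10 × 0.90)]² / 0.15² = 99.5, so 100 per arm.

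The figure reproduces (power 80.2%). The article gives no power, SD or correlation for quality of life, so everything below rests on assumptions.

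**2. Detectable difference at one visit.** Assumed: SD 20 points, two-sided alpha 0.05, power 80%, normal scores, baseline-to-follow-up correlation r.

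- Unadjusted comparison of means: (1.96 + 0.8416) × 20 × √(2/n)
- Mann-Whitney: the same divided by √(3/π) = √0.955
- Baseline-adjusted: the same multiplied by √(1 − r²)

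| Respondents per arm | Means, unadjusted | Mann-Whitney | Adjusted, r=0.2 | r=0.5 | r=0.6 |
|---|---|---|---|---|---|
| 100 | 7.92 | 8.11 | 7.76 | 6.86 | 6.34 |
| 70 (assumed attrition) | 9.47 | 9.69 | 9.28 | 8.20 | 7.58 |

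The first part of each gain (8.11 to 7.92 at 100 per arm) comes only from assuming normal scores. The rest comes from the baseline. At r=0.2 the baseline contributes little: 7.92 to 7.76. At r=0.5 it contributes about one point. In patient terms, 1/(1 − r²) is 1.04 at r=0.2, 1.33 at r=0.5 and 1.56 at r=0.6.

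**3. Multiplicity, if each visit is tested.** The article does not say that it will be. If each of the two priority domains were tested at each of five visits, there would be 10 tests. With independence, the chance of at least one false positive is 1 − 0.95¹⁰ = 40%. By simulation, with correlation 0.6 between visits, 0.5 between domains at the same visit, and their product (0.3) across domain and visit, it is about 28%.

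**4. Selective non-response.** A simulation used 100 patients per arm, no true difference, correlation 0.5 between visits and about 29% missing at the last visit. Missingness depended on the previous score in one arm only. A Mann-Whitney test on responders rejected in 13.4% of trials, with a spurious difference of about 0.15 SD. When missingness was unrelated to score in both arms, with about 27% missing, it rejected in 4.8%. This is a deliberately unfavourable pattern. It shows the direction of the risk and does not forecast its size in this trial.

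**5. Does the missing-data paragraph cover this?** Its main method, covariate-adjusted Poisson regression with robust variance, suits a yes/no outcome such as leakage and not a questionnaire scale. Multiple imputation could be applied to questionnaire scores and followed by a rank test. But it is planned as a sensitivity analysis, so even if it extends to quality of life, the main comparison stays as named.

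**The case against.** The strongest reply is that the sentence is short and should not be over-read.

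- **It does not say raw scores, one visit at a time.** A rank test on change from baseline, or on each patient's average over visits, would fit the wording and use some of the extra information. This stands in part. The text mentions neither option, and a test on change scores would still not use the repeated visits jointly. A reader might infer ten separate tests and a 28% to 40% false-positive risk. The document does not state per-visit testing, so those figures are conditional.
- **Choice of time point is commonly left to the analysis plan.** Agreed, and the missing time point is not the point here. The test itself is a stated choice.
- **Multiple imputation is planned.** It is, with no restriction to leakage, so it would be wrong to say that missing questionnaires are ignored. But it does not alter the main analysis.
- **Effect sizes will be visible.** Arm-level summaries are planned, and a Hodges-Lehmann estimate with an interval can accompany the rank test. So the complaint is only that a between-arm interval is promised for the primary outcome alone.
- **The test is valid.** With complete data it is a sound comparison of randomized arms, and leaving out baseline or hospital costs efficiency without introducing bias. For skewed, bounded scores it may even be more efficient than a normal-theory method. All of this stands and limits the weight of the point.

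A reader might also infer that baseline forms are completed after patients learn their allocation, since Table 1 puts both in one column and the trial is open. The documents give no order within that column, so they do not support this.

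**Conclusion.** The point holds as an inexpensive improvement to a secondary analysis. The named method fits poorly with six assessments per patient. The cost is mainly precision: under SD 20 and 100 per arm, a detectable difference of 8.1 points where baseline adjustment would give 7.8 (r=0.2), 6.9 (r=0.5) or 6.3 (r=0.6). Major surgery lies between baseline and follow-up, so a low correlation, and hence a small gain, is possible. The second cost is exposure to selective non-response at the later visits, whose size cannot be judged from the article.

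SD, correlation, respondent numbers and normality are all assumed. It would go too far to call the planned test invalid or the quality-of-life results biased. The leakage analysis and the total of 200 patients are unaffected.

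**What to change.** In the Statistical analysis section, replace the quality-of-life sentence along these lines:

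- Analyse each scale with a linear mixed model for repeated measures, with arm, visit, arm by visit, baseline score and hospital, using all available forms.
- Report between-arm mean differences with 95% confidence intervals.
- Name one main contrast for each of the two priority domains, for example the average difference over the 3- to 24-month visits, and treat other domains and visits as supportive.
- Keep the Mann-Whitney test as a sensitivity analysis.
- State whether the multiple-imputation sensitivity analysis includes quality of life, and confine the Poisson approach to binary outcomes.

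The cost is analysis wording only: no extra forms, visits or patients. There are two downsides. The model applies normal theory to bounded scores, which the retained rank test helps to check. It also assumes data missing at random, which does not by itself deal with scores cut off by death, so the plan should say how those are handled. The change should be fixed before outcome data are compared by arm.
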